### Randomization process

The random sequence generation process and the participants’ allocation to the intervention conditions will be run automatically by the online platform. After completing the baseline assessment, parents will be randomized and allocated to one of the conditions through an automated computerized randomization program, with an equal allocation ratio (1:1); the online intervention will be immediately available for parents after the allocation.

Parents will be blinded to which condition they were assigned during the trial. Participants are aware that the two interventions will be run and compared, and the tasks involved in each will be summarily reported, but they are not informed about the study’s hypothesis. The use of an active comparator intervention as a control condition will reinforce the blinding mechanism: parents will receive a similar intervention regarding the sequence of contents, duration, and the information available, but without the behavior change techniques intended to change parents’ and children’s behaviors (i.e., knowledge-based intervention). Researchers will be blinded to group allocation. Because of the intervention’s nature, which is programmed to be delivered automatically by the online platform according to the parent’s pace and answers, researchers do not participate directly in the intervention and cannot change its course.

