#### Control condition

Parents assigned to the active comparator condition receive the same information as the experimental conditions regarding nutritional guidelines for young children and effective/ineffective parental feeding practices. However, this control group does not have access to interactive activities (e.g., quizzes) or self-regulation strategies during and between sessions (e.g., tailored feedback, goal setting, monitoring of the child’s food intake, and parental feeding practices).

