### Study procedures

Once parents access the site and complete the registration, they are invited to identify their reasons for participating in the intervention and receive information about the program’s characteristics and the feeding situations in which the intervention can support them. Then, parents are asked to read the online informed consent form, including detailed information about the program (e.g., study objectives, eligibility criteria, information about the study groups and tasks required in each one, random allocation procedures, data collected during the study). If parents agree to participate, the consent form is sent automatically to the participant’s email, and they are directed to the baseline assessment protocol, to be completed within 2 weeks. Parents are also asked to record their child’s food and portion intake for 3 days (two weekdays and one weekend day). The days to perform the 24-h food recalls are randomly chosen by the app, and parents receive a notification the day before. After completing these tasks, each parent is allocated automatically to one condition, and session 1 is released. At the end of the program, parents receive a notification to fill the post-intervention evaluation protocol within a maximum of 15 days. A similar procedure occurs 3 and 6 months after the intervention.

There will be no special criteria for discontinuing or modifying allocated interventions. Parents of children with any medical condition that may affect dietary behavior or growth (e.g., food allergies or intolerances, chronic health conditions) or receiving other professional counseling can participate in the program. They are encouraged to discuss any doubts about the recommendations provided by the program with the child’s assistant, to better suit their child’s condition; the healthcare professional can contact the investigators through the project email.

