Possible limitations of our study protocol include the following: We anticipate most participants to be highly interested and motivated parents, with children with fewer feeding issues, possibly with a higher education level. We also expect most participants will be mothers. Although this is a common issue in parental nutrition interventions, children’s dietary patterns can be influenced by the other caregivers’ practices and the overall home food environment. Only the enrolled participant can complete the tasks and answer the questionnaires and food records. Also, all the measurement outcomes are reported by parents, including the objective measures (i.e., 24-h food recall, children’s and parents’ BMI), and those reports rule the self-regulatory strategies throughout the sessions. The RCT’s intervention arm is quite demanding due to the regular monitoring between sessions and the tasks required during the sessions. This experience can be challenging for some overwhelmed, time-constrained, or less motivated parents and might contribute to a high dropout rate. Also, a lack of direct contact with the research team can decrease parents’ involvement in the program. Although a design with an intervention arm and an active control condition comply with high-quality methodological standards, it also can lead to a less-expressive difference between conditions.

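### Parents are described as blinded to their condition, but the disclosed tasks of each arm probably reveal it; only the hypothesis is withheld, and all six primary outcomes are parent-reported

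*Protocol article*

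**What the plan says.** Under Randomization process the protocol article makes a plain claim: "Parents will be blinded to which condition they were assigned during the trial". It goes on: "Participants are aware that the two interventions will be run and compared, and the tasks involved in each will be summarily reported". What it says is withheld is the hypothesis: "they are not informed about the study’s hypothesis". An active comparator is offered as support for the masking, because "parents will receive a similar intervention regarding the sequence of contents, duration, and the information available". Researchers are also said to be blinded.

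Under Study procedures, the consent form is read before the baseline assessment and before allocation. Its listed contents include the study objectives and "information about the study groups and tasks required in each one". A copy is emailed to the parent.

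Under Control condition, the comparator arm gets the same nutritional and feeding-practice information, but "this control group does not have access to interactive activities" and has none of the self-regulation elements (tailored feedback, goal setting, monitoring).

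In the Discussion, the methodological paragraph describes the design as having a reduced risk of bias. The limitations paragraph concedes that "all the measurement outcomes are reported by parents", but does not mention knowledge of allocation.

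**The concern.** A participant is blinded to allocation only if what they know beforehand and what they then experience do not let them work out their arm. Here parents are told what each arm has to do and then either do it or do not. That leaves masking of the hypothesis, which is a weaker property and should not carry the other's name.

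The distinction matters because the parent is the outcome assessor. If parents know their arm, reporting may differ between arms for reasons other than real change in the child's diet or in feeding practices. Experimental parents set goals, record against them and receive personal feedback on their records; control parents do not. A reader who accepts the blinding statement would give this possibility too little weight when interpreting a difference between arms.

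**Working it through.** No stated figure is at issue, so the check is a comparison of sections.

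1. **What parents are told, and when.** Randomization process says "the tasks involved in each will be summarily reported". Study procedures places the description of the groups and their tasks in the consent form. The order there is consent, baseline questionnaires, three days of food recall, then allocation. Disclosure therefore precedes randomization.

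2. **Whether the arms differ in what is disclosed.**

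| Element | Experimental | Control |
|---|---|---|
| Nutritional guidelines; effective and ineffective practices | Yes | Yes (same information) |
| Sequence of contents and duration | Reference | Described as similar |
| Quizzes and other interactive activities | Yes | No |
| Tailored feedback | Yes | No |
| Goal setting | Yes, from session 1 (Table 1) | No |
| Monitoring between sessions (food recall; practices and habits) | Yes; needed before the next session opens | No |

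The entries come from Table 1 and the text under Experimental condition, from Control condition, and from Randomization process. The first two rows are matched. The last four are tasks or features that a parent meets directly, and they are what separates the arms.

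3. **What follows.** A parent who knows that one arm sets goals and records food intake between sessions, and who is or is not asked to do this, can probably identify the arm. The baseline recall does not help to tell the arms apart, because everyone completes it before allocation. The between-session recall and the goals do.

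4. **What remains masked.** The hypothesis is not disclosed. Even this may be partial, since the study objectives are in the consent form.

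5. **Who supplies the primary outcomes.** Under Outcome measures there are three intake measures from the 24-h recall (vegetables, fruit, sugar-sweetened foods and beverages) and three scores from the Food Parenting Practices Questionnaire: 3 + 3 = 6. The parent completes all six. Researchers do not rate any of them, so researcher blinding protects none of these measurements.

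**The case against.** The strongest case on the other side has five parts.

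- **Disclosure may be thin.** The tasks are reported only in summary and the consent form is not shown. A reader might infer that allocation is obvious to every parent from the first or second session. The documents do not establish that; they support probable identification. This limits the wording, but does not restore the claim of blinding.
- **The comparator is active and matched.** Similar sequence, duration and information should bring expectations closer together, which is a real strength. It does not conceal whether the disclosed tasks are present.
- **Both arms learn what is desirable.** A reader might infer that only experimental parents are taught which answers meet the guidelines. Control condition says otherwise: both arms receive the same information on guidelines and practices. What differs is personal feedback, goals and monitoring, so any difference in reporting would have to arise through those. That remains possible, but it is a narrower mechanism.
- **Parent report is already a listed limitation.** This is so, and the reader is warned about self-report. The missing part is its link to probable knowledge of the arm. The risk-of-bias sentence describes the design in general and does not cite parent blinding, so it needs qualifying rather than removing.
- **Masking is hardly feasible in a self-guided behavioural programme.** This is fair, and the design need not change. It is a reason to describe the situation accurately.

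**Conclusion.** The statement that parents are blinded to their condition is wrong as written. It conflicts with the disclosure described in the same section and under Study procedures, combined with the arm differences under Control condition. The documents support masking of the hypothesis only, and the six primary outcomes should be read as assessed without allocation blinding.

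The conclusion rests on one inference: that the consent summary names the main distinguishing tasks (goals, feedback, between-session monitoring). The text points that way but does not show the form.

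A reader might want to attach a size, for example by assuming a reporting shift and dividing it by a detectable difference. The documents give no such shift, and the ratio would change with the number taken as analysed (130 after the assumed dropout, or all 260 under intention-to-treat). It would also measure neither the bias in the estimate nor the false-positive risk. No magnitude should be quoted. The point concerns what can be concluded from the results; it does not alter the test, the sample size or the design.

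**What to change.** - In Randomization process, replace the claim with: parents are not blinded to allocation; they are not told the study hypotheses. Keep the blinding claim for researchers only, and describe the active comparator as matching content and duration.
- In the Discussion, qualify the reduced-risk-of-bias statement by noting that participants, who are also the outcome assessors, are not blinded to allocation.
- Extend the existing limitation on parent report, and commit the trial's conclusions to the same statement: effects rest on parent report with probable knowledge of allocation.
- If a perceived-allocation or expectation question is added after the intervention, report it descriptively by arm. Do not use it to stratify the primary effects. It is measured after randomization and may be influenced by the intervention, so contrasts within its levels are not randomized comparisons. If most parents do identify their arm, it would also vary little within arms.

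The cost is a few sentences and, if wanted, one app question. The downside is a less favourable risk-of-bias rating. The change makes the reporting accurate; it does not remove any bias.

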### Study procedures

Once parents access the site and complete the registration, they are invited to identify their reasons for participating in the intervention and receive information about the program’s characteristics and the feeding situations in which the intervention can support them. Then, parents are asked to read the online informed consent form, including detailed information about the program (e.g., study objectives, eligibility criteria, information about the study groups and tasks required in each one, random allocation procedures, data collected during the study). If parents agree to participate, the consent form is sent automatically to the participant’s email, and they are directed to the baseline assessment protocol, to be completed within 2 weeks. Parents are also asked to record their child’s food and portion intake for 3 days (two weekdays and one weekend day). The days to perform the 24-h food recalls are randomly chosen by the app, and parents receive a notification the day before. After completing these tasks, each parent is allocated automatically to one condition, and session 1 is released. At the end of the program, parents receive a notification to fill the post-intervention evaluation protocol within a maximum of 15 days. A similar procedure occurs 3 and 6 months after the intervention.

There will be no special criteria for discontinuing or modifying allocated interventions. Parents of children with any medical condition that may affect dietary behavior or growth (e.g., food allergies or intolerances, chronic health conditions) or receiving other professional counseling can participate in the program. They are encouraged to discuss any doubts about the recommendations provided by the program with the child’s assistant, to better suit their child’s condition; the healthcare professional can contact the investigators through the project email.

Several procedures aim to facilitate sample maintenance throughout the program. The platform sends automatic emails when parents take longer than expected to complete the tasks, reminding them about the timings and goals chosen in the sessions, giving new opportunities, or motivating parents to login into the platform. Parents can send an email if they experience any technical difficulty. The IT team will monitor the platform utilization to identify and solve any digital implementation problem. There is no anticipated harm for trial participation. Participants will receive a 20-euro compensation voucher after accomplishing the program and the two follow-up evaluation protocols.

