## Methods

### Study design

To study the efficacy of the *SmartFeeding4Kids*, we adopted a randomized, controlled, superiority trial, with two-arm with four repeated measures design (Figs. 1 and 2). After baseline assessment, parents are randomly assigned to one of the two conditions: one experimental group (*SmartFeeding4Kids*) and one active comparator group. After finishing the program, parents complete the same evaluation protocol immediately and 3 and 6 months after the intervention. The study’s report follows the Consolidated Standards of Reporting Trials (CONSORT) statement [18] and the SPIRIT 2013 statement [19].

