Between sessions, parents are asked to complete a 24-h food recall regarding children’s food intake on a day of their choice and answer questions about parental practices and feeding habits related to the goals chosen in each session. These records are available 3 days after completing each session and are asked to be accomplished during the following week. A new session is only accessible once parents have seen the last session’s contents and performed the tasks proposed between sessions. During this time, parents also receive a notification to remember the core message and the session’s goals [30]. Participants are rewarded with points and badges when specific targets are reached (e.g., when a selected goal is reached, when the feedback shows progress in performing a specific behavior compared with the last session), or when completing specific tasks (e.g., see a specific content).

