#### Development of the *SmartFeeding4Kids* app

We designed and developed an application in Portuguese, the *SmartFeeding4Kids app*, to deliver all the intervention components and manage the trial. It can be used on web browsers or as an app on a mobile device and includes seven sessions that cater components from randomization, onboarding, 24 h food recall, delivery of information, personalized feedback to data collection (e.g., study questionnaires), and logging. Parents are guided through the program with new contents unblocked depending on the previous step and time.

The application was designed to be appealing and engaging. The visual design includes lively colors and several professional drawings of vegetables and fruits as characters (Fig. 3). Information boards are presented as slideshow animations where these characters give textual feedback illustrated with carefully designed visualizations. *Aba*, an avocado avatar, welcomes and accompanies parents in the application, guiding, informing, and motivating them through the sessions. Charts are presented to illustrate each session’s performance based on food diaries. To further fuel parents’ engagement, badges are given when they complete pre-defined achievements. Examples of badges are finishing a session, interacting with content, and daily logins, among others. In addition, to promote discoverability, we have introduced hidden rewards as special badges that are not visible before being won (e.g., a badge for filling the food recall meals along the day instead of all at the same time). Notifications and reminders are automatically sent via email to congratulate users for their performance, remind them of pending tasks, and announce new content.

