### Statistical analysis

We will use intention-to-treat principles, with the participants being analyzed in the group in which they were allocated in the randomization process, independently of whether they had completed all measurement time points and/or the intervention. First, an evaluation of missing data mechanisms will be performed to inform which imputation strategy should be applied between multiple imputations (MI) and maximum likelihood estimation (FIML). Assuming the data are missing at random, a sensitivity analysis will be included, considering the whole samples vs. samples with complete data separately.

A descriptive analysis of demographic data and outcome variables at baseline will be performed for parents’ and children’s characterization purposes; the samples in each condition group will also be compared for all dimensions studied. Repeated measures analyses will be used to analyze the differences between condition groups and measurement time points over time regarding primary outcomes, adjusting for potential covariates. To study parents’ dropout predictors, we will first assess the differences between completers, early and late dropouts regarding demographic data, and all variables at baseline. The relationships between parents’ and children’s dimensions with dropout rates will be assessed. We will then conduct a binomial logistic regression to predict the overall dropout. The analysis of individual health trajectories regarding parents’ and children’s variables evolution throughout the intervention will be studied using mixed models. The *p* value will be corrected according to the number of primary outcomes considered in each statistical analysis.

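### Follow-up assessments and the voucher are tied to finishing the program, and no route to assessment is given for parents who stop, although intention-to-treat analysis is promised

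*Protocol article*

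**What the plan says.** **Trigger for assessment.** Study design: "After finishing the program, parents complete the same evaluation protocol immediately and 3 and 6 months after the intervention". Study procedures repeats the trigger: "At the end of the program, parents receive a notification to fill the post-intervention evaluation protocol within a maximum of 15 days". The later visits follow suit: "A similar procedure occurs 3 and 6 months after the intervention".

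**Reaching the end of the program.** Under Experimental condition: "A new session is only accessible once parents have seen the last session’s contents and performed the tasks proposed between sessions". For the app as a whole: "Parents are guided through the program with new contents unblocked depending on the previous step and time".

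**Incentive.** Study procedures: "Participants will receive a 20-euro compensation voucher after accomplishing the program and the two follow-up evaluation protocols".

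**Analysis.** The Statistical analysis section commits to intention to treat, with parents kept in their allocated group "independently of whether they had completed all measurement time points and/or the intervention". Missing values are to be handled by multiple imputation (MI) or full-information maximum likelihood (FIML). Missing at random is assumed, and the sensitivity analysis compares the whole sample with the complete cases.

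**Expected dropout.** Power and sample size allows for 50%, which takes 130 parents to 260. The Discussion says that the "intervention arm is quite demanding due to the regular monitoring between sessions and the tasks required during the sessions" and that this may contribute to high dropout.

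**The concern.** The analysis plan treats completing the intervention and supplying outcomes as separate matters. The procedures join them. If assessments are sent when a parent finishes, a parent who stops at session 3 never reaches the stated trigger and has no paid reason to be assessed. The reminders described concern overdue program tasks and returning to the platform. No assessment date is counted from randomization.

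Two things are at stake. First, parents with only a baseline record say almost nothing directly about the post-baseline difference between arms, so a model has to extrapolate their outcomes from finishers. Comparing the whole sample with complete cases does not probe that step, since both analyses can be wrong in the same direction when stopping depends on something unmeasured. Second, the arms differ in burden. The control condition has no monitoring, goal setting or interactive tasks, so the parents who finish may be a more selected group in the experimental arm. The between-session food and practice records cannot fill the gap, because only the experimental arm has them.

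**Working it through.** **1. The plan's own figure.** Evaluable 130, dropout 0.50: 130 / (1 − 0.50) = 260, as stated. The inflation therefore counts on 260 × 0.50 = 130 parents without usable follow-up.

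**2. How many could be affected.** If all of that dropout is stopping before the end of the program, 130 of 260 parents never reach the trigger. The article does not split the 50%, and it distinguishes early from late dropouts. Some of the 130 may finish and miss only a later assessment, so 130 is the upper bound at the planned rate.

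**3. Finishers' effect against the effect in all randomized parents.** Let *c* be the share finishing, *E* the finishers' effect and *k* the fraction of *E* that non-finishers obtain (*k* is an assumption).

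All-randomized effect = *cE* + (1 − *c*)*kE*. With *c* = 0.5:
- *k* = 0: 0.50*E*
- *k* = 0.5: 0.75*E*
- *k* = 1: 1.00*E*

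**4. Selection that differs by arm, under no true effect.** Assumptions not in the article: 40% finish in the experimental arm and 60% in control; finishing is decided by an unmeasured trait, standard normal, correlated *t* with the outcome.
- Finishers: 0.4 × 130 = 52 and 0.6 × 130 = 78.
- Mean trait among the top share *p* is φ(z)/*p*, with z the cut-off. For *p* = 0.4: 0.3863 / 0.4 = 0.966. For *p* = 0.6: 0.3863 / 0.6 = 0.644. Difference 0.322.
- Residual variance after adjusting for baseline at the stated correlation of 0.35: 1 − 0.35² = 0.8775.
- SE = √[0.8775 × (1/52 + 1/78)] = 0.168.
- Type I error = Φ(−1.96 + bias/SE) + Φ(−1.96 − bias/SE).

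*Case A: the trait is unrelated to baseline.* Bias = 0.322*t*.
*Case B: the trait is correlated t with baseline too.* Baseline adjustment removes part of the bias; approximately, bias = 0.322*t* × (1 − 0.35).

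| *t* | A: bias (SD) | A: type I error | B: bias (SD) | B: type I error |
|---|---|---|---|---|
| 0.2 | 0.064 | 6.7% | 0.042 | 5.7% |
| 0.3 | 0.097 | 8.9% | 0.063 | 6.6% |
| 0.4 | 0.129 | 12.0% | 0.084 | 7.9% |

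A simulation of case B gave biases of 0.043, 0.064 and 0.093 SD and type I errors of 5.3%, 6.6% and 8.8%, close to the approximation. The overall range is roughly 0.04 to 0.13 SD and 6 to 12%. The test is at an uncorrected 5%. The article plans to correct for the number of primary outcomes, so these rates show the direction and order of the problem and are not the planned error rate.

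**The case against.** **The exclusion is inferred.** The lock is stated for sessions, not for evaluation protocols, and no sentence says that parents who stop are never contacted. The flow diagram and assessment schedule are not visible in the text reviewed, and an article condenses a fuller protocol. This stands as a limit on certainty. It does not remove the point, because the trigger is stated twice in the same terms and no alternative is offered.

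**Stopping need not mean losing every outcome.** A reader might infer that the two are the same event, or that 130 parents are expected to have no post-baseline data. The article does not support either. The dropout rate is a general one, and late dropouts may have given some follow-up.

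**The intention-to-treat result is not simply a completer effect.** That is another tempting inference. Motivation, self-efficacy, barriers, education, weight concern and temperament are all recorded at baseline. MI or FIML using them can correct for selection on measured variables. What remains is selection on unmeasured factors, whose size is unknown.

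**Timing by arm.** One might infer that assessments fall later in the experimental arm because it has more tasks to clear. The Randomization process section describes the control intervention as similar in duration. Unequal timing is possible but not shown.

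**Dropout is already acknowledged.** The sample is doubled for it, the Discussion lists burden as a limitation, and the voucher is meant to reward full participation. Doubling the sample protects precision; it does nothing about bias from who is measured.

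**Conclusion.** The point holds in a limited form. Followed as written, the procedures give non-finishers no route to assessment and so undercut the promise to analyse parents regardless of intervention completion. This is a stated trigger, not a detail left for the analysis plan, and outcomes never collected cannot be recovered at analysis.

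Up to 130 of 260 parents could be affected at the planned dropout. Their follow-up values would depend on missing at random, an assumption that the planned sensitivity comparison leaves untested. The all-randomized effect could lie anywhere from 0.5 to 1.0 times the finishers' effect, depending on what non-finishers gain. The false-difference figures are an illustration that depends on the assumed 40%/60% completion and the unmeasured trait. With equal selection in both arms, that spurious difference would be zero. The conclusion also rests on the platform doing what the text says. If it already invites parents who stop, the fault is in the description.

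**What to change.** - Have the app send all three evaluation protocols to every randomized parent at fixed times from randomization (the planned program length, then 3 and 6 months later), whether or not the sessions are finished.
- Make the voucher depend on completing the assessments instead of the program.
- Record program completion and assessment completion as separate variables.
- If non-finishers are already contacted, correct Study design and Study procedures, including the voucher sentence, to say so.

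**Cost.** Notifications are already automated, so this is a change of triggers and a short amendment. Extra vouchers come to at most about 130 × 20 = 2,600 euros at the planned dropout. There are two real downsides. For slow finishers, the assessment described as immediate becomes a fixed-time one, which changes what it measures. And because recruitment began in July 2021, parents already enrolled may be on a different schedule from later ones, so the schedule followed should be recorded for each parent and handled in the analysis.
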